### Retention and withdrawal

We will seek to follow up all participants except those who expressly withdraw from the study. Withdrawal at the participant level will be considered if any of the following occurs: participant is lost to follow-up; withdrawal of consent; or death. All withdrawals will be recorded and the reason will be specified.

### Adverse events

Only study-related adverse events (AE) will be reported. Information regarding AEs (including incidence, duration, seriousness, severity, relationship to treatment, and action taken) will be recorded throughout the study. If AEs occur, the first concern will be the safety of the study participants. AEs will be graded by the research staff completing the assessments and/or residential facility physicians at each site for severity and relationship to study treatment. Study-related AEs will also be reported to the site’s Human Research Ethics Committee.

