### Randomization

An independent statistician will perform the randomization sequence generation using a computer-generated list. For logistical reasons and to minimize confounding effects, stratified cluster randomization designs will be used to randomize participants by residential aged care facility (stratified by size and region) to the intervention (ROC) or control (usual care) arm. Participants in the same aged care facility will all be assigned to the same study arm. The allocation sequence will be concealed from the research assistants enrolling and assessing participants. Residential care facility staff, the research study coordinator, and the eye health professionals delivering ROC will not be masked to the group allocation as this is impractical.

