### Usual care

Residents with VI in the usual care group will be referred for an evaluation to the eye care service associated with the facility or a practitioner of their choice.

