### Sample size

Pilot data collected from 31 participants residing in a single-site aged care facility were used to guide power calculations for this study ([name], [name], [name], [name]: Vision Optimisation in Residential Care: A pilot study, unpublished, 2011). They showed that following correction, 30% of participants had improved distance vision by at least two lines and 30% of the participants improved by ≥ 0.2 Log units on a text reading chart for near vision. Therefore, the sample size calculation is based on achieving a 30% improvement in VA (near and distance vision) at two- and six-month follow-up visits in the intervention group compared to controls. The anticipated effect size will be ~ 0.65 based on our pilot work. At a significance level of 0.05, with 38 participants in each arm (overall total of 76 participants) we will have 80% power to detect a group difference. We assume an intra-cluster correlation coefficient (ICC) within-facility of 0.05 which corresponds to the levels found in similar work in nursing homes [28]. The inflation factor (or design effect) will be estimated using the following formula: Inflation factor = 1+ (number of patients per facility [50]-1) X ICC = 3.5. To take cluster design into account, we need a total sample size of 266 [76 × 3.5]. However, to adjust for non-compliance with the intervention (~ 10% due to people who seek vision care on their own in the usual care arm, or people who refuse the intervention in the intervention arm) and loss to follow-up (~ 25% largely due to deaths), the effective sample size needs to be increased by a factor of 1.48 (1/0.90 × 1/0.75) resulting in an initial enrolment requirement of 395 individuals.

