### Cost-effectiveness analysis

We will perform an incremental cost-effectiveness analysis from the payer perspective. Direct intervention costs (labor, material and supplies, and contracted services costs) associated with delivering the intervention over the one-year period will be collected and follow a cost collection approach described elsewhere [29]. The incremental costs of the intervention will need to account for any vision services received by the usual care group and any differences in costs for non-vision related services that may be an indirect result of the intervention. Information will be collected for any participants who fall or are hospitalized, transferred to high care or die. Aggregating these costs over the six-month period and adding them to the direct costs of the ROC intervention group, will allow the total medical costs for the intervention and the usual group to be quantified. The incremental cost-effectiveness ratio (ICER) will be calculated using the estimated mean difference in effect (EQ-5D-3L) and the estimated mean difference in costs between the intervention and the control groups. The ICER indicates the average incremental cost to gain one additional quality-adjusted life year (QALY). Cost data are likely to be skewed. Therefore, using non-parametric bootstrapping, 1000 replicates [30] will be generated to estimate the 95% confidence intervals around the ICER. A cost-effectiveness acceptability curve (CEAC) [31] will be used to show the probability that the intervention is cost-effective for a range of monetary values that a decision maker might be willing to pay for a unit change in QALYs. Cost-effectiveness will initially be quantified assuming that QALYs are only sustained for one year, but an assessment will also be made based on the assumption that they continue to accrue each year for the expected remaining life years in the study sample. Additional one-way (and n-way) deterministic sensitivity analyses will be performed to examine the effect of changing one (or n) of the model parameters.

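### Adverse-event reporting is limited to study-related events, so the AE report cannot fairly compare the arms, and hospitalizations, transfers to high care and unrelated serious AEs have no stated safety comparison

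*Protocol article*

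**What the plan says.** The Adverse events section opens with the reporting rule: "Only study-related adverse events (AE) will be reported". It then says that AE information, including seriousness, "relationship to treatment, and action taken) will be recorded throughout the study", with no restriction by arm. The filter therefore acts on reporting, not on recording. On who applies it: "AEs will be graded by the research staff completing the assessments and/or residential facility physicians at each site for severity and relationship to study treatment".

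The Randomization section says that facility staff, the study coordinator and the eye professionals delivering ROC "will not be masked to the group allocation as this is impractical". The Usual care section says that control residents "will be referred for an evaluation to the eye care service associated with the facility or a practitioner of their choice". The Intervention section gives ROC residents an on-site examination and, as needed, spectacles, cataract surgery, ophthalmologist referral and low vision rehabilitation, with transport funded by the study.

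Clinical events also appear in four other places:

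- Person-centered outcomes and Statistical analysis: falls are taken from facility incident systems and compared between arms.
- Retention and withdrawal: "Withdrawal at the participant level will be considered if any of the following occurs", and death is one of the listed reasons.
- Missing data: the proportion and reasons of withdrawal are compared between arms by a Chi-squared test.
- Cost-effectiveness analysis: "Information will be collected for any participants who fall or are hospitalized, transferred to high care or die".

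**The concern.** A harms report compares arms fairly only if an event has the same chance of entering it in either arm. Here entry depends on a judgement of relatedness to study treatment, and only one arm receives a substantial study treatment. An event in usual care has little to be related to. The same event in ROC may be attributed to spectacles, surgery or transport.

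Usual-care residents can still receive eye care. They are referred for it, the Sample size section allows for some seeking it themselves, and the cost analysis accounts for vision services they use. A surgical complication could therefore be reported in one arm and left out in the other.

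The judgement is also partly made where allocation is known. At stake is whether readers who must decide on adopting ROC, which includes a surgical pathway, can see its harms set against those of usual care.

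**Working it through.** **1. What the filter does to a comparison.** Let p be the true risk of an event, equal in both arms, and q the share of events labelled related. Expected reported events per arm = n × p × q. With equal p, the ratio of reported events (ROC to usual care) is q(ROC) / q(usual care). It reflects labelling, not risk, and a larger sample does not correct it.

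**2. Size of the trial.** The planned enrolment reproduces. An effect size of 0.65 at two-sided 0.05 and 80% power needs 38 per arm, or 76 in total. Then 76 × 3.5 = 266, and 266 / (0.90 × 0.75) = 394.1, against 395 stated. Assuming that 1:1 randomization of facilities gives equal numbers of residents, n = 395 / 2 = 197.5 per arm.

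**3. Illustration.** The article gives no rate for hospitalizations, transfers or AEs. The one related figure is "loss to follow-up (~ 25% largely due to deaths". If 50% to 100% of that loss is death (assumed), the risk is 0.25 × 0.5 = 12.5% to 25%. I borrow this range as an assumed risk for a common serious event, and assume q = 5% to 20% in ROC and 0 in usual care.

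| | Lowest case | Highest case |
|---|---|---|
| True events per arm | 197.5 × 0.125 = 24.7 | 197.5 × 0.25 = 49.4 |
| Reported, ROC | 24.7 × 0.05 = 1.2 | 49.4 × 0.20 = 9.9 |
| Reported, usual care | 0 | 0 |

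So 25 to 49 events in each arm, with no true difference, would appear as about 1 to 10 against 0.

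**4. Which events still have a between-arm comparison?**

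| Event | Recorded | Stated comparison that does not depend on relatedness |
|---|---|---|
| Falls | Facility incident systems | Yes, secondary outcome at six months |
| Deaths | Withdrawal reason; cost data | Yes, as a reason for withdrawal |
| Hospitalizations | Cost data | None as safety |
| Transfers to high care | Cost data | None as safety |
| Other AEs judged unrelated, including serious ones | AE records | None |

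The comparison of deaths sits under Missing data, where death is one withdrawal reason among several and is not presented as a harm. It is still a comparison between arms.

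**The case against.** The strongest reply is that the trial does not depend on its AE report for safety. Falls and deaths are compared without regard to relatedness, and hospitalizations are at least collected. A reader might infer from the reporting rule that no valid between-arm safety comparison is left, or that any imbalance in deaths is hidden. The documents do not support either reading. The expected losses (0.25 × 395 = about 99, of which about 49 to 99 are deaths if 50% to 100% of losses are deaths) are therefore not a measure of what is lost, because those deaths enter the comparison of withdrawal reasons.

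Three further points deserve weight.

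- The reporting sentence speaks of study-related events, while study treatment appears only in the grading sentence. The article does not define the first term, and the usual-care referral could be counted as part of the study. That is why usual care can contribute little, and not strictly nothing. Still, the only relatedness judgement the section describes is against study treatment.
- Some graders may be masked. The research staff doing assessments are not on the unmasked list, and the allocation sequence is concealed from the research assistants. The masking concern applies to the facility physicians, if they count as facility staff. The differential filter does not depend on unmasking.
- Layout of AE tables can be left to a full protocol or SAP. That would excuse silence, but here the article states a rule. Nor is the rule only about ethics committee notification: the section's last sentence adds that as a further step.

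**Conclusion.** The point holds in limited form. Followed as written, the AE report is filtered differently by arm and cannot fairly compare harms. Hospitalizations, transfers to high care and other serious AEs judged unrelated have no stated safety comparison, although the data are recorded.

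This conclusion rests on the stated rule and on the contrast between the two arms' care. The count of about 1 to 10 against 0 shows direction and scale only: its event risk, its labelling shares and the equal arm sizes are assumptions. The number of hospitalizations and transfers affected cannot be derived from the article. No primary or secondary outcome analysis is affected.

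**What to change.** Replace the opening sentence of the Adverse events section with:

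*All recorded adverse events, and all deaths, hospitalizations and transfers to high care, will be reported by randomized arm regardless of judged relationship; relationship will be given as an additional column.*

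Name as sources the data already gathered under Adverse events, Retention and withdrawal, and Cost-effectiveness analysis. Cross-refer to the falls analysis in Statistical analysis so that falls are read alongside the other harms.

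The cost is a change of wording, a few tables and a longer list of mostly unrelated events. No new data collection is needed for these items. Complications of eye procedures in usual care are different: no section says they are collected systematically, and recruitment, which began in June 2014, is expected to finish by 1 December 2018. Include them only where already recorded, and state that limitation beside the table.

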**Methods/design:**

This protocol describes a multicentered, prospective, randomized controlled trial. A total of 395 participants with distance vision < 6/12 (0.30 LogMAR) and/or near vision N8 (1.00 M) or worse will be recruited from 38 urban and rural aged care facilities across Victoria, Australia. Aged care facilities will be randomized (1:1) to one of two parallel groups. Participants in the ROC group will receive a comprehensive and tailored eye care pathway that includes, as necessary, refraction and spectacle provision, cataract surgery, low vision rehabilitation, and/or a referral to an ophthalmologist for funded treatment. Usual care participants will be referred for an evaluation to the eye care service associated with the facility or an eye care provider of their choice. The primary outcome will be presenting near and distance vision assessed at the two- and six-month follow-up visits, post baseline. Secondary outcomes will include vision-specific quality of life, mobility, falls, depression, and eye care utilization at two and six months. An incremental cost-effectiveness analysis will also be undertaken.

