### Participant flow

All prospective participants who sign a study consent form will undergo a screening examination. When inclusion and exclusion criteria are met, the participant will be invited to complete a pre-intervention face-to-face baseline assessment with a research assistant. Following the baseline assessment, participants will receive the ROC intervention or usual care. All participants will be invited to complete follow-up assessments at two and six months after baseline visits.

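### The adverse event section lets outcome assessors, who appear meant to be unaware of allocation, judge relatedness to treatment; this can unmask them for a whole facility

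*Protocol article*

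**What the plan says.** The Randomization section of the protocol article says: "The allocation sequence will be concealed from the research assistants enrolling and assessing participants". It then names those who will know the arm. They are the facility staff, the study coordinator and the providers of the intervention; of the last it says that "the eye health professionals delivering ROC will not be masked to the group allocation as this is impractical". The assessing research assistants are not on that list. The same section makes the facility the unit of allocation: "Participants in the same aged care facility will all be assigned to the same study arm".

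The Adverse events section assigns the grading: "AEs will be graded by the research staff completing the assessments and/or residential facility physicians at each site for severity and relationship" to study treatment. It says that information on events, including "relationship to treatment, and action taken) will be recorded throughout the study". It also limits reporting to events judged to be study-related.

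Under Participant flow, baseline is a "pre-intervention face-to-face baseline assessment with a research assistant". No different assessor is named for follow-up. The abstract states: "The primary outcome will be presenting near and distance vision assessed at the two- and six-month follow-up visits, post baseline". Under Person-centered outcomes, questions on the use of spectacles and low vision aids are put at those same two visits to intervention-arm participants only.

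**The concern.** Relatedness is a judgement about treatment. In this trial the treatment is an open care pathway: spectacles, cataract surgery, referral to an ophthalmologist, or low vision rehabilitation. Someone asked whether an event arose from it will usually need to know whether the resident was in the ROC arm and what was provided. If the assessor is told, masking is lost. If not, the relatedness grade is poorly informed. Either way the two sections do not fit together.

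What is at stake is detection bias. Nothing in the article masks the residents, and the facility staff are expressly unmasked, so the assessors' ignorance of the arm is the main protection left. Chart acuity depends partly on effort and prompting. The quality of life instruments are given by interview, and the final depression rating on the Cornell scale rests on the rater's impression. With allocation by facility, a leak about one resident is a leak about all participants at that site.

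**Working it through.** The point is about roles, so the check sets the sections side by side. The only arithmetic is the size of a facility.

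1. **Are the assessors meant to be masked?** The Randomization section speaks literally of concealing the sequence, which could mean concealment at enrolment only. However, it extends this to those who assess participants, and it goes on to list the people who will not be masked without including them. Masked assessment is therefore the natural reading, though it is implied and never stated.

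2. **Are the graders the same people?** The Adverse events section identifies its first group of graders by their task, carrying out the assessments. Participant flow gives the baseline assessment to a research assistant and names nobody else for follow-up. The two groups very probably overlap, although the terms differ.

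3. **Does the grading call for the arm?** Severity does not. Relatedness usually does. Because only related events are reported, relatedness also decides what enters the safety record, so it has to be judged for any event that might be kept or dropped.

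4. **Can grading come before outcome measurement?** Events are recorded throughout the study and outcomes are measured at two and six months. An event graded between baseline and two months precedes both visits. One graded between the two visits precedes the second. One graded at six months after testing precedes no further measurement of that resident, but it may precede those of other residents at the same facility. The article fixes no order within a visit.

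5. **How far does one judgement reach?** Planned enrolment is 395 and there are 38 facilities (abstract; Settings and study participants). Average per facility = 395 / 38 = 10.4. Applying the 25% loss to follow-up from the Sample size section, 395 × 0.75 / 38 = 7.8 would still be measured at the end. The figure of 50 residents per facility in the design-effect formula is not used here, since 38 × 50 = 1,900 does not match an enrolment of 395.

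6. **How often would it happen?** This cannot be computed. The article gives no adverse event rate and no split of grading between assessors and physicians.

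**The case against.** The best case for the plan has five parts.

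- **The wording is permissive.** The physicians may do all the grading, which is the remedy proposed below. This stands, and it means that unmasking is possible but not built in. The same wording equally lets the assessors do all the grading.
- **No order is set.** A reader might infer that the plan unmasks assessors before they measure the primary outcome. The documents do not support that. It follows only if an assessor does the grading, learns the arm in doing so, and has measurements still to make at that facility.
- **Relatedness can sometimes be judged without the arm**, either conditionally or because the facts rule treatment out. This stands for some events, but does not cover an event whose relation turns on what was provided.
- **Operational detail may be in the full protocol, version 2.2, which is not shown.** That would excuse silence. Here the article makes a positive statement about who grades, and it conflicts with another positive statement.
- **Adverse event grading is not the main leak.** The device-use questions are asked only in the intervention arm at both follow-up visits, and acuity is tested with whatever glasses the resident wears, possibly including study-supplied ones. If the same assistants do this work, the arm may be exposed more regularly than by any adverse event. This stands, and changing the adverse event sentence alone would not secure masking.

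A reader might also infer a particular bias in acuity. The documents give no figure from which one could be derived, and they say that distance acuity is tested by established procedures, which limits examiner influence.

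**Conclusion.** The two sections conflict and should be reconciled. As written, the Adverse events section permits assessors whom the Randomization section implies should be unaware of allocation to judge relatedness to treatment. That can unmask them for a whole facility, about 10 enrolled participants on average, before later acuity, quality of life and depression measurements.

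The conclusion rests on three assumptions: that masked assessment was intended, that the assessing assistants are among the graders, and that a grader will at times need or be told the arm. The figure of 10 further assumes that the assessor covers the whole site; the number affected is smaller where some residents have already completed their measurements. If masked assessment was not intended, the Randomization section is the text that needs correcting.

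This is a modest, avoidable weakness in trial conduct. It does not show that the primary comparison is biased.

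**What to change.** Amend the Adverse events section so that outcome assessors record only the facts of an event (what happened, when, for how long, what was done). Assign the relatedness grade to the facility physician, whom the section already names, or to other unmasked staff such as the study coordinator. The article does not say outright that these physicians count as facility staff, so it should state that they are unmasked.

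In the Randomization section, say explicitly that the people who measure outcomes at two and six months are masked to allocation.

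Have unmasked staff ask the device-use questions. Asking them after all outcome measurements at a visit is a weaker alternative: it protects that resident's current visit, but not the six-month visit or other residents at the site who are still to be measured by the same assessor.

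The cost is a few sentences and a little more time from physicians or unmasked staff. Sample size, analysis and eye care pathways are unchanged.
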